### Measures

The primary outcome is change in PA, which is assessed at baseline, 3 months, and 9 months using triaxial accelerometers worn at the right hip during the day over the course of 7 days and a self-administered questionnaire. Participants received the self-administered questionnaire and accelerometer at their introductory event at baseline (T0), after 3 months (T1) at their tenth group meeting, and after 9 months (T2) at their last monthly meeting. Further, due to cost issues, a random subsample of 114 participants (equally distributed across the intervention groups) underwent additional anthropometric, physical fitness, and cognitive tests to assess secondary outcomes at all 3 time points. Physical fitness was assessed using gait speed via a 4-meter walk test [29], handgrip strength using a dynamometer [30], and cardiovascular fitness using the 2-minute step test [31]. Additionally, participants’ weight was assessed using a scale. Attention and inhibition were assessed using a cognitive test (Simon task) [32].

Data from the objective measures of physical fitness and cognitive performance (Mini Mental State Examination and executive function test) will be preprocessed using customized MATLAB routines and analyzed using multivariate generalized linear models. Data for physical fitness and cognitive performance assessed at baseline and after the 10-week intervention during the first funding phase and in the subsample of participants during the second funding phase will be pooled to increase power for data analysis and to meet sample heterogeneity. Further, the larger sample size will enable us to conduct subgroup analyses with respect to motivational stage, activity behavior, and social engagement.

All participants underwent a short version of the Mini Mental State Examination during their first weekly group meeting [33]. Motivational stages to engage in recommended PA (endurance, strength, flexibility, and balance training), social-cognitive predictors for behavior change, and psychosocial factors (eg, quality of life, depression) were assessed in the self-administered questionnaire (for further detail on the instruments included in the questionnaire, see Table 1).

**Table 1 table1:** Measures assessed in the self-administered study questionnaire.

Outcome measure		Instrument/scale	Time of assessment

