### Study Design

After determination of eligibility, study participants were randomized to either an IT-based intervention or a print-based intervention (see Figure 1). In the first group, 30% were randomly selected to receive a PA tracker in addition to access to the website. Weekly time slots were randomly assigned to both intervention groups. Then, we had participants choose appointments according to their personal time constraints without knowing which intervention group they were assigned to. All intervention groups were offered weekly group sessions, and participants were encouraged to attend each of them. Two weeks before the intervention started, participants in all groups attended an introductory event where they were informed about the study background and procedures. On this day, data collection also started, and participants received the activity tracker and questionnaires for the first time (T0). They were also briefed about their randomization to one of the intervention groups and the existence of the other groups. Therefore, they were not blinded. Participants were given the choice to remain in their intervention group or to cross over to the other group after 3 months (and a 10-week intervention period). With that, a crossover design with the following possible combinations was generated: IT-IT, print-print (matched), or IT-print and print-IT. Preferences regarding the intervention material assessed retrospectively at the 9-month follow-up will be taken into account when analyzing intervention effects later in the study. Research staff members conducting the study were not blinded, and the statistician will not be blinded when analyzing the data.

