### Analytic Strategy

Effects of time and group (main outcomes: subjective and objective measures of PA) will be examined in multivariate analyses. In addition, covariates, such as gender, age, and preferences regarding intervention material, and individual contextual factors (eg, living or social environment) will be taken into account. Furthermore, we will analyze how the intervention enables study participants to change their behavior by running mediation analyses. The estimated target sample size of 390 participants for this study is based on the results of 2 recently published studies on PA in adults [27,28] that reported a mean 111 weekly minutes (SD 116.8 weekly minutes) of MVPA and an intervention effect of an increase in MVPA of 77 minutes per week. However, in a conservative (or realistic) approach, we assumed that the mean increase in MVPA in our study will reach only 40 minutes/week. To detect such a difference between the intervention and control groups with a power of 80% at an alpha of .05 (two-sided), a net sample size of 150 subjects for each group is required. Assuming a loss to follow-up from T0 to T1 of 20-25% (ie, ca. 23%), it is necessary to initially recruit 390 study participants (ie, 195 per group at baseline). Assuming another 20% loss to follow-up from T1 to T2, we expect that approximately 240 individuals at T2 will self-select to one of the 4 groups: IT-IT, print-print, IT-print, or print-IT. Should participants self-select equally into each group (n=60), we will still be able to detect the mean difference of 77 minutes/week [28] between each group, by means of an appropriate post hoc test that is adjusted for multiple comparisons.

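### Accelerometer and unblinded self-reported activity at two follow-ups share primary status without ranking or alpha allocation, while the formal sample size is for one MVPA comparison

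*Protocol article*

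**What the plan says.** **Primary outcome (Measures).** "The primary outcome is change in PA, which is assessed at baseline, 3 months, and 9 months using triaxial accelerometers", worn "over the course of 7 days and a self-administered questionnaire". The two instruments stand in one sentence with equal standing.

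**Analysis (Analytic Strategy).** "Effects of time and group (main outcomes: subjective and objective measures of PA) will be examined in multivariate analyses". No order is given between the instruments or between 3 months (T1) and 9 months (T2).

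**Sample size (Analytic Strategy).** The cited studies "reported a mean 111 weekly minutes (SD 116.8 weekly minutes) of MVPA". The authors assume a difference of 40 minutes/week and conclude that "with a power of 80% at an alpha of .05 (two-sided), a net sample size of 150 subjects for each group is required". About 23% loss from T0 to T1 raises this to 195 per group, 390 in total, so the net number applies at T1. The text does not say whether this MVPA is accelerometer-measured or self-reported.

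**Multiplicity (Analytic Strategy).** The one adjustment mentioned is a post hoc test among the four groups that participants select themselves into at T2 (60 each, 77 minutes/week).

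**Blinding (Study Design).** Participants were told their allocation: "Therefore, they were not blinded". The statistician is not blinded either.

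**The concern.** The article defines its primary outcome in two places, and both definitions cover two instruments. The measurement schedule adds two follow-ups. The formal calculation covers one variable, one contrast and one alpha. So the outcome definition and the sample size do not describe the same test.

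Two things are at stake. The first is error control: nothing prevents the favourable instrument or time point from being presented as the primary result. The second is interpretation: if the accelerometer and the questionnaire disagree, the plan does not say which one answers the question.

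Self-report is the weaker candidate here. Participants know their arm, and the self-monitoring tools differ. According to the Interventions and Study Design sections, the IT arm has a daily as well as a weekly overview, and 30% of that arm have a tracker. The print arm has a weekly paper diary. Reported activity could therefore move differently by arm without a matching change in behaviour.

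Table 1 leaves the questionnaire outcome itself open. It lists a modified leisure-time exercise questionnaire at T0, T1 and T2. It also lists self-generated training items at T1 and T2 only, which cannot give a change from baseline.

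**Working it through.** **Inputs from Analytic Strategy:** SD 116.8 and difference 40 minutes/week of MVPA; two-sided alpha .05; power 80%; net 150 per group; about 23% loss T0-T1; 20% loss T1-T2. The correlations in step 3 are assumptions, since the article gives none.

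**1. The plan's own figures.**
- n per group = 2 × (116.8/40)² × (1.960 + 0.842)² = 2 × 8.526 × 7.849 ≈ 134 (135 by t-test). The stated 150 is not reproduced. It is larger than needed, with power Φ(40/(116.8 × √(2/150)) − 1.960) = Φ(2.966 − 1.960) ≈ 84.3%. The present point does not depend on this difference.
- Loss: 150/(1 − 0.23) = 194.8, so 195 per group and 390 in total, which reproduces. At T2, 300 × 0.80 = 240, which also reproduces.
- Each of these steps belongs to a single test at .05.

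**2. Family-wise error, if separate unadjusted tests at .05 were run, any one counted as success, and the tests were independent.**
- Two instruments at T1: 1 − 0.95² = 9.75%.
- Two instruments × two follow-ups: 1 − 0.95⁴ = 18.5%.

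**3. The same with correlated tests** (multivariate normal, 1,000,000 draws per row):

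| Assumed correlation between instruments | Assumed correlation between time points | Four tests | Two instruments at T1 |
|---|---|---|---|
| 0.3 | 0.5 | 16.9% | 9.6% |
| 0.3 | 0.7 | 15.6% | 9.5% |
| 0.5 | 0.5 | 16.2% | 9.0% |
| 0.5 | 0.7 | 14.9% | 9.1% |
| 0.7 | 0.7 | 13.6% | 8.4% |
| 0.8 | 0.8 | 12.0% | 7.8% |

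**4. Cost of keeping several primary tests** (Bonferroni, same SD and difference):

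| Primary tests | Alpha each | Power at 150 per group | Net n per group for 80% | Recruited at 23% loss |
|---|---|---|---|---|
| 1 | .05 | 84.3% | 134 | already met by 390 |
| 2 | .025 | 76.6% | 163 | 424 |
| 4 | .0125 | 68.0% | 191 | 498 |

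**5. Reach of the existing adjustment.** Four self-selected groups give six pairs. With 60 per group and 77 minutes/week, power at .05/6 is 83.5%, so the T2 statement is arithmetically sound if the groups are equal. It covers pairs of groups at T2. It does not cover instruments or the choice between T1 and T2.

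**The case against.** The strongest reply is that the article states no success rule. A reader might infer that the trial can be declared positive on any of four results, or that its type I error is already above 5%. The text supports neither. A multivariate analysis of time and group could be one joint test, and details of alpha within the model may sit in an analysis plan that is not shown. Nor is four a count the plan gives: at T2 it describes four self-selected groups with an adjusted post hoc test, not one unadjusted comparison per instrument. This stands, and it makes the error rates conditional.

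A reader might also infer that the sample size was built on accelerometer MVPA. Analytic Strategy does not name the instrument. It also words the difference as one between an intervention and a control group, although the Discussion lists the lack of a control group as a limitation. MVPA and T1 can be taken from the calculation; the accelerometer cannot.

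Third, both arms are active, use the same pyramid-shaped diary, receive weekly goal feedback and are offered group sessions. Nothing in the article shows that self-report shifts by arm, or in which direction. That limits the bias argument to a possibility, but the lack of blinding and the difference in tools are stated.

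The objection does not supply a hierarchy. The article itself names the primary outcome, and names it as two instruments, so this is a definition fixed badly rather than a detail left to another document.

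**Conclusion.** The point holds in limited form. Accelerometer and self-reported activity, at 3 and 9 months, share primary status with no ranking of instruments or time points and no alpha divided between them. The formal sample size serves one MVPA comparison: "with a power of 80% at an alpha of .05 (two-sided"), with its net number at T1.

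The size of the problem depends on a decision rule that the article does not state. If any one of several separate unadjusted tests may count as success, family-wise error is about 8-10% for two instruments at T1. For four tests it is 18.5% under independence and about 12-17% under the assumed correlations (0.3-0.8 between instruments, 0.5-0.8 between time points). Under a single joint test these rates would not apply, but the question of what to conclude from discordant instruments would remain.

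Timing makes the gap more serious. The Results section says data collection ended on January 31, 2020 and analysis began in February 2020, and the statistician is unblinded. An instrument or time point left open can be settled after results are seen.

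**What to change.** In Measures and Analytic Strategy, name one primary outcome: accelerometer MVPA in minutes/week at T1, adjusted for T0, IT versus print as randomised, two-sided .05. MVPA and T1 match the sample size. The accelerometer is chosen because participants are not blinded and the self-monitoring tools differ by arm; say so, rather than imply that the calculation specified it.

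Make accelerometer MVPA at T2 and questionnaire activity at T1 and T2 secondary, and name the questionnaire measure. In the same edit, reconcile the intervention-versus-control wording of the sample size with the two active arms.

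Record the date of this decision relative to the start of analysis and to any sight of results by arm. If a document that predates the analysis already names a single primary outcome, cite it.

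The cost is about one sentence in each section plus the dated record. Self-report loses primary status. No participants are added, and at the planned 150 per group the single test keeps about 84% power under the plan's own SD and difference.

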**Physical activity**			
	Physical activity	Godin Leisure-Time Exercise Questionnaire (modified) [34]	T0^a^, T1^b^, T2^c^
	Recommended endurance, strength, balance, and flexibility training at follow-up	Self-generated items	T1, T2
	Stage of change regarding physical activity (endurance, strength, and balance + flexibility training, respectively)	HAPA^d^, stage of change, 3 items [35,36]	T0, T1, T2
	Intention to engage in physical activity	HAPA, intention, 2 items [36-38]	T0, T1, T2
	Self-efficacy regarding physical activity	HAPA, self-efficacy, 5 items [36,38]	T0, T1, T2
	Positive and negative outcome expectancies regarding physical activity	HAPA, outcome expectancies, 4 items [36,38,39]	T0, T1, T2
	Planning for physical activity	HAPA, planning, 6 items [38,40]	T0, T1, T2
	Habit strength regarding physical activity	Self-Report Habit Index, 2 items [41]	T0, T1, T2
	Physical self-description	PSDQ^e^ [42]	T0, T1, T2
**Physical environment**			
	Physical activity and neighborhood environment	Physical Activity Neighborhood Environment Scale [43]	T0
	Walking environment	Neighborhood Scales, walking environment [44]	T0
**Social support, social activities**			
	Social support for engaging in physical activity	Activity-related support by family and friends (modified) [45,46]	T0, T1, T2
	Social activities	Florida Cognitive Activities Scale (modified) [47,48]	T0, T1, T2
**Health behaviors**			
	Subjective age	Difference score (perceived physical age - chronological age = subjective physical age) [49]	T0, T1, T2
	Subjective health status	WHOQOL-BREF^f^, 1 item [50,51]; SF-36^g^, 1 item [52]	T0, T1, T2
	Health-related quality of life	EQ-5D-3L^h^ [53,54]	T0, T1, T2
	Objective health	Diseases and medication use (modified) [55]	T0
	Falls	EFST^i^ (modified) [56]	T0, T1, T2
	Fear of falling	GFFM^j^ [57]	T0, T1, T2
	Diet	FFQ^k^ (modified) [58]	T0, T1, T2
	Alcohol consumption	AUDIT-C^l^ [59]	T0, T1, T2
	Smoking behavior	Smoking Behavior Questionnaire, 1 item [60]	T0, T1, T2
	Stage assessment of smoking behavior	HAPA, stage of change [35,36]	T0, T1, T2
**Quality of life and well-being**			
	Quality of life	WHOQOL-BREF, 1 item [50,51]	T0, T1, T2
	Depression	CES-D^m^ [61]	T0, T1, T2
**Previous experiences with technology**			
	Use of computers/smartphones/apps	Self-generated items	T0, T1, T2
	Technology commitment	Technology Commitment Scale [62]	T0, T1, T2
**Use of, acceptance of, and satisfaction with interventions**			
	Use and acceptance of various components of the interventions (website and printed material), attendance of the offered group sessions, and overall satisfaction with the interventions	Self-generated items	T1, T2
	Preference regarding intervention material at baseline (retrospective)	Self-generated item	T2
	Reasons for crossing over or not crossing over after 3 months	Self-generated items	T2

^a^Baseline.

^b^3-month follow-up.

^c^9-month follow-up.

^d^HAPA: Health Action Process Approach.

^e^PSDQ: Physical Self-Description Questionnaire.

^f^WHOQOL-BREF: World Health Organization Quality of Life-BREF.

^g^SF-36: Short Form 36.

^h^EQ-5D-3L: 3-level version of the EQ-5D.

^i^EFST: Elderly Fall Screening Test.

^j^GFFM: Geriatric Fear of Falling Measurement.

^k^FFQ: Food Frequency Questionnaire.

^l^AUDIT-C: Alcohol Use Disorders Identification Test Short Version.

^m^CES-D: Centers for Epidemiologic Studies Depression Scale.

Anthropometric information, as self-reported in the questionnaire, included height in cm (only T0) and weight in kg (all time points). Sociodemographic information was assessed at baseline only, using items of the German Health Interview and Examination Survey for Adults [63] for date and country of birth, gender, native language, family and relationship status, living situation, education, employment status, and monthly net household income. Employment was assessed using one item of a questionnaire for assessing seniors’ demographic and sociostructural data in Germany [64]. In addition, the self-administered questionnaire at T1 and T2 includes self-generated items regarding adherence to the PA recommendations (weekly minutes of endurance, balance, and flexibility training and weekly units of muscle strength training per muscle group) and attendance of the offered group sessions. Furthermore, use and satisfaction with the intervention material and content are assessed with the following self-generated items: frequency of general use; use of different intervention components reporting using a 5-point Likert scale from “never” to “daily”; perceived helpfulness of intervention components, intervention content, and structure of weekly meetings rated on a 5-point Likert scale ranging from “not helpful at all” to “very helpful”; potential knowledge gained and perceived benefits of PA using “yes” and “no” response options; and whether participants would recommend the intervention to family and friends, answered using open-ended questions. Data on the reasons for dropping out of the study and the reasons for crossing over or not crossing over to the respective other intervention group were also collected.

### Interventions

To simplify and further develop the IT-based intervention implemented during the first funding phase and to translate it into a print-based intervention, 9 focus groups consisting of former participants of the previous intervention (n=1), other members of the target group (n=32), and stakeholders in communities such as members of senior citizen organizations and advisory boards (n=12) were held in May and June 2018. Participants of these focus groups were recruited via a press release and already established contacts to the stakeholders. Focus group discussions consisted of two parts. First, intervention materials used in the previous study and materials and health brochures for PA promotion developed by other researchers; federal agencies, such as the Federal Ministry of Health (BMG); or health insurance agencies were discussed with regard to their suitability for PA promotion in inactive older adults. In this context, the participants were invited to vote for the material they liked most and to justify their decision. Second, using the World Café method, participants were asked to discuss the following questions in small groups of 4-5 participants:

From your perspective, what are the key aspects of healthy aging?Which topics related to healthy aging should be addressed in an intervention in order to reach physically inactive older adults?What do inactive older adults need to be able to successfully participate in a PA intervention?Which barriers need to be overcome and what would be helpful to these participants?What would be motivating for inactive older adults for maintaining a healthy lifestyle?

The focus group discussions and votes for or against certain intervention materials were protocolled by the moderating researchers, and the resulting recommendations and requirements for the intervention material were applied when refining the existing IT-based intervention and when translating the IT-based intervention into a print-based intervention. Results consisted of recommendations regarding font size and color, amount of text to read, appropriateness of content (eg, inclusion of recommendations regarding diet, sleep hygiene, or pain management), and considerations with regard to the target group (eg, mobility, physical limitations, and the role of social support, loneliness, and wellbeing).

Both interventions are based on self-regulation theory [65,66] and principles of behavior change (eg, shaping knowledge, feedback and monitoring, goals and planning, social support, comparison of behavior, rewards) [67] and are designed to facilitate a physically active lifestyle by promoting regular self-monitoring of PA. Participants of both the IT-based and print-based interventions received PA recommendations based on WHO recommendations for this age group regarding endurance training (at least 150 minutes per week of moderate exercise, at least 75 minutes of intensive exercise, or a combination of both, in bouts of at least 10 minutes), strength training (at least 2 units per week for the 8 main muscle groups on non-consecutive days), and balance and flexibility training (at least 4 units per week for 5 minutes) [2]. Depending on gender, participants were provided with different brochures (online and offline) outlining exercises for different difficulty levels and displaying pictures of male or female older adults modeling these exercises.

They also received a weekly PA diary in the form of a pyramid to subjectively track their PA behavior. Intervention material was printed for the print-based intervention group, while participants in the IT-based group received access to the exercise brochure and diary on a website and were provided the opportunity to download a smartphone app containing similar features. On the website or Android app, as well as in the printed diary, weekly feedback on whether participants reached PA goals was provided by displaying the amount of minutes or units exercised in the according week, as well as units required to reach the goal (ie, WHO recommendations for moderate exercise time, flexibility, and strength training). In addition to the weekly feedback, the website and Android app also provided participants a daily overview of PA. In the daily overview, participants had access to more detailed information about the exercises for the individual muscle groups, whereas in the weekly overview (in the IT-based and print-based interventions), only information about the progress towards the weekly goals was provided (see Figure 2). The app also allowed participants to record exercises without an active internet connection and synchronized recordings with the website, once the device was connected to the internet again. Participants in the IT-based intervention group who used the PA tracker in addition to the website or app also monitored their PA behavior objectively via synchronization of data regarding daily steps with the website. Data from the PA trackers will be analyzed based on methods presented in Meyer et al [68] to gain insights into participants’ PA behavior in everyday life during the time between assessments.

